#### Safety and data monitoring

An independent data and safety monitoring board (DSMB) composed of oncologists, gastrointestinal surgeons, and statisticians is responsible for reviewing trial data, including adverse events (AEs) and drop-outs, at least twice a year. If any unexpected AEs happen or any types of AEs occur more frequently than our own Chinese database and most authors reported, members of the DSMB will consider early closure of this trial according to relevant Chinese laws and regulations. AEs in this trial are evaluated by using NCI-CTC as a secondary outcome. Severe adverse events (SAEs) in this trial include death, disability, and prolonged hospitalization. Both AEs and SAEs will be recorded in CRFs and the DSMB will be informed within 24 hours.

#### Sample size and statistics

The LC-ACEC trial aims to identify the non-inferiority of 3-year DFS of patients in the low-dose capecitabine adjuvant chemotherapy group versus the approved-dose group. We assumed that a background 3-year DFS was 60 % and predefined the non-inferiority margin of the hazard ratio (HR) as 1.30. When 456 events of the primary endpoint 3-year DFS occur, the efficacy analysis will be conducted. We chose a statistical power of 0.80 and a significance level of 0.05 (two-sided). Given the 10 % drop-out for elderly patients, the calculation yielded a sample size of 926 patients (463 in each arm) [11, 25].

The intention-to-treat analysis will be applied with all patients who undergo randomization in this trial. With regard to survival data, HRs with 95 % confidence intervals (CIs) will be presented by Kaplan-Meier survival estimates. Additionally, Cox proportional HRs with 95 % CIs will be calculated on the basis of subgroups of different characteristics (that is, age, sex, stratum, and Charlson comorbidity index), which can identify the influence of competing risk factors for the outcome event. For the primary outcome of 3-year DFS, the non-inferiority will be concluded if the upper limit of the 95 % CI is not more than 1.30 (predefined non-inferiority margin). As for other outcomes, proportions will be compared by using chi-squared test, and continuous data will be analyzed by *t* test. All the statistical analyses will be conducted by using SPSS version 20 software (SPSS, Inc., Chicago, IL, USA).

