### Outcomes

#### Primary outcome

The primary outcome of the LC-ACEC trial is 3-year disease-free survival (DFS), which is calculated from the date of randomization to whichever of the following events occurs first in 3 years: local recurrence, metastasis, death from any causes, or development of other malignances.

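### The 456-event trigger does not fit a primary endpoint that counts only 3 years: under the plan's own assumptions about 353 to 370 events are expected, giving about 69-71 % power instead of 80 %

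*Protocol article*

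**What the plan says.** The Primary outcome section of the Protocol article defines 3-year DFS as time "calculated from the date of randomization to whichever of the following events occurs first in 3 years": local recurrence, metastasis, death or another malignancy.

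The section Sample size and statistics then gives the design figures:
- The control assumption: "We assumed that a background 3-year DFS was 60" per cent.
- The margin: the authors "predefined the non-inferiority margin of the hazard ratio (HR) as 1.30".
- The error rates: "We chose a statistical power of 0.80 and a significance level of 0.05 (two-sided").
- The timing of the analysis: "When 456 events of the primary endpoint 3-year DFS occur, the efficacy analysis will be conducted".
- After a 10 % allowance for drop-out, "the calculation yielded a sample size of 926 patients (463 in each arm").
- The decision rule: "the non-inferiority will be concluded if the upper limit of the 95 % CI is not more than 1.30".

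Study design and setting gives a start in January 2015 and an expected end in 2023. The article states neither the accrual period nor a hazard after year 3.

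**The concern.** The trigger names the same endpoint that the Primary outcome section limits to 3 years. If 60 % of patients are event-free at 3 years, about 40 % are expected to have a countable event. For 926 patients that is well short of 456.

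Two things are at stake. The primary analysis is tied to a count that the plan's own assumptions do not produce. And if the analysis is run once everyone has 3 years of follow-up, its power is below the stated 80 %, so a low dose that is truly equal would fail to show non-inferiority more often than the planned one time in five. The choice between capped and uncapped DFS also decides which events enter the hazard ratio. In an open-label trial whose analysts know the allocation, that choice should be settled before the data are seen.

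**Working it through.** **Inputs.** From Sample size and statistics: margin HR 1.30, two-sided 0.05, power 0.80, 3-year DFS 60 %, drop-out 10 %, N = 926 at 1:1, trigger 456 events. From Primary outcome: events count only within 3 years. Assumption: true HR = 1.0, which is not stated but is the value that reproduces 456.

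**1. Reproduce the plan's event number (Schoenfeld).**
d = 4 × (1.960 + 0.842)² / (ln 1.30)² = 456.1. The stated 456 is reproduced.

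**2. Events expected under the 3-year cap, both arms at 60 % DFS.**
- No drop-out: 926 × 0.40 = 370.4.
- Drop-out of 10 % spread exponentially over 3 years: event hazard λ = −ln(0.60)/3 = 0.1703 per year, drop-out hazard μ = −ln(0.90)/3 = 0.0351 per year. Event share = λ/(λ+μ) × (1 − 0.60 × 0.90) = 0.829 × 0.46 = 0.381. Events = 926 × 0.381 = 353.
- Drop-outs contribute nothing (lower bound): 926 × 0.90 × 0.40 = 833.4 × 0.40 = 333.4.
- For comparison, low-dose arm exactly at HR 1.30 and no drop-out: its 3-year DFS is 0.60^1.30 = 0.515, so events = 463 × (0.40 + 0.485) = 410. This is still short of 456.

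**3. Chance of reaching the trigger.** With 926 patients and event probability 0.40, the binomial probability of at least 456 events is about 8 × 10⁻⁹.

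**4. Power at the capped event count.** Power = Φ(√(d/4) × ln 1.30 − 1.960).

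| Events d | √(d/4) × ln 1.30 | Power |
|---|---|---|
| 456 (stated) | 2.801 | 80.0 % |
| 370 (no drop-out) | 2.525 | 71.4 % |
| 353 (drop-out spread over 3 years) | 2.465 | 69.3 % |
| 333 (lower bound) | 2.395 | 66.8 % |

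**5. What 456 events within 3 years would require.**
- Patients: 456 / 0.40 = 1,140 evaluable; 1,140 / 0.90 = 1,267 randomized.
- Or, with 926 patients, a pooled 3-year DFS of 1 − 456/926 = 51 % without drop-out, or 1 − 456/833.4 = 45 % if drop-outs contribute nothing.

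**6. If events after year 3 counted.** This takes 833 evaluable patients, uniform accrual (assumed) and minimum follow-up after the last patient enters.
- Constant hazard, 3.5 years' accrual + 3 years' follow-up: about 456 events.
- Hazard halved after year 3 (assumed): 3 + 5 years gives about 461 events, 4 + 4 about 444, and 5 + 3 about 426. By the formula in step 4, power is about 80 %, 79 % and 77 %.

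**The case against.** The strongest counter-argument is that the 3-year wording is only a label and that ordinary event-driven DFS was meant. An event-count trigger, a hazard-ratio margin, six-monthly visits after year 2 with no stated end and a trial running to 2023 all fit that reading. Step 6 shows that 456, 60 %, 10 % and 926 can then agree, given suitable accrual and follow-up. This stands as a possible intention and is why one of the two fixes is purely a clarification. It does not remove the point: no sentence states the uncapped reading, the Primary outcome section gives the window in words ("whichever of the following events occurs first in 3 years"), and the trigger repeats the capped name.

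A second defence is that a one-sided 0.05 test would give 77-81 % power with 333 to 370 events. The article specifies two-sided 0.05 and a 95 % confidence interval rule, so this does not rescue the stated design.

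Some stronger readings go too far:
- A reader might infer that the trigger can never occur. The 60 % is an assumption and not a ceiling on events; a 3-year DFS of 51 % or lower would reach 456.
- A reader might take 67 % as the expected power. It requires that drop-outs contribute no events at all, whereas under the planned intention-to-treat analysis they contribute until they are censored.
- A reader might infer that the cut-off date is left to discretion. The full protocol or an analysis plan may fix it, and a condensed article's silence on a fallback is not a fault.

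**Conclusion.** The point holds as a contradiction between the endpoint definition and the sample-size basis. The event number itself is correct. What does not follow, under the stated 3-year cap, is that 926 patients will supply it. With 60 % 3-year DFS and a true HR of 1.0, about 353 to 370 events are expected and power is about 69-71 %, with 67 % as a lower bound, against the stated 80 %. A truly equal low dose would then miss non-inferiority in about 29-31 % of trials (at most 33 %) rather than 20 %.

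The result depends on reading the 3-year window as written. It would be wrong to conclude that 926 is irreconcilable with 456 events on every reading: without the cap the two can agree, depending on accrual and on the hazard after year 3, neither of which is stated.

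**What to change.** Reconcile the Primary outcome section with Sample size and statistics in one of two ways, before outcome data are examined.

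(a) **Remove the 3-year limit.** Define DFS as time from randomization to first event, with all events counted up to the data cut-off at 456 events. Report the 3-year Kaplan-Meier DFS per arm as a descriptive estimate. Add a calendar backstop at the planned 2023 end, and state the accrual assumption, the hazard assumed after year 3, and the power at the event count expected by then. It should not be promised that 926 patients suffice: step 6 shows this depends on those two assumptions.

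(b) **Keep the 3-year limit.** Replace the event trigger with analysis once all patients have been followed for 3 years, and restate power as about 69-71 %, with 67 % as a lower bound.

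Either way the change is an amendment to the endpoint and sample-size wording. Visits after year 3 are already planned. The price is a possibly later analysis under (a), or a lower stated power under (b).

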### Randomization and blinding

All participants fulfilling the inclusion criteria will be randomly allocated into either the low-dose or the approved-dose group. We use a computer-generated blocked randomization sequence with the block size of four according to the previous published trial conducted in WCH [21]. Patients are randomly assigned by stratification of disease stage (stage II or III) and primary tumor site (colon or rectum). To achieve allocation concealment, opaque envelopes with sequential numbers are adopted to seal the assignment and are accessible only for investigators not involved with this trial. After enrollment of each patient, the envelope is sent to an independent investigator, who is not involved in patient evaluation, to assign participants to either the low-dose or the approved-dose group. This is an open-label trial; thus, patients, investigators, and data analysts are aware of the group assignment.

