### Intervention

About 4 to 8 weeks after surgery [20], patients in the low-dose group will take oral capecitabine after breakfast and dinner at the dose of 1,000 mg/m^2^ bid, and patients in the approved-dose group will receive the dose of 1,250 mg/m^2^ bid. Each treatment cycle consists of 14 days of capecitabine administration and then 7 days of rest.

Colon cancer patients in both groups are supposed to take eight circles of treatment in total (24 weeks) [22]. Eight circles of treatment will also apply to rectal cancer patients who had neoadjuvant radiotherapy (regimen 1 in Fig. 2). For rectal cancer patients without neoadjuvant radiotherapy, we defined high-risk patients who need concomitant radiochemotherapy (RCT) as patients with positive circumferential resection margin (CRM+) or with lymph node metastasis (N+), and they will receive a total of five circles of chemotherapy [13]. The RCT serves as the third circle and lasts about 6 weeks [13]. During the RCT period, the irradiation dose is 45 Gy/25 fractions, and the capecitabine dose is reduced to 800 mg/m^2^ bid [23] (regimen 2 in Fig. 2). According to the toxic events, the dose of capecitabine will be adjusted following the drug instruction of Xeloda® [15]. Any patients who have intolerable toxic or side effects will discontinue the medication.

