#### Secondary outcome

Several secondary outcomes are adopted in this trial. In addition to the primary outcome of 3-year DFS, the 3-year overall survival is calculated from the randomization to the date of death from any causes. Toxic and side effects during adjuvant chemotherapy will be closely observed and evaluated by using National Cancer Institute Common Toxicity Criteria (NCI-CTC) version 2.0. Based on the toxic and side effects, we will keep every record of modification or discontinuance of capecitabine and calculate the completion rate of the treatment as one of the key secondary outcomes. Moreover, QoL data are recorded by using a Chinese translation of European Organisation for Research and Treatment of Cancer Core QoL Questionnaire C30 (EORTC QLQ-C30) [24].

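### Completion rate and toxicity are compared with a plain chi-squared test although randomization is stratified by stage and site: valid, but mildly conservative if rates differ between strata

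*Protocol article*

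**What the plan says.** In the protocol article, Sample size and statistics gives one rule for all secondary proportions: "As for other outcomes, proportions will be compared by using chi-squared test". It names no strata or adjustment for them. The 5 % level and 80 % power in that section belong to the disease-free survival (DFS) calculation; no level, power or expected difference is given for completion or toxicity.

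Randomization and blinding describes a "computer-generated blocked randomization sequence with the block size of four" and adds: "Patients are randomly assigned by stratification of disease stage (stage II or III) and primary tumor site (colon or rectum"). That makes four strata, with the arms close to equal inside each.

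Intervention links treatment to the same two factors, and to two others:
- Colon: "Colon cancer patients in both groups are supposed to take eight circles of treatment in total (24 weeks").
- Rectum after prior radiotherapy: "Eight circles of treatment will also apply to rectal cancer patients who had neoadjuvant radiotherapy".
- Rectum without prior radiotherapy, high risk: "patients with positive circumferential resection margin (CRM+) or with lymph node metastasis (N+), and they will receive a total of five circles of chemotherapy". The third cycle is radiochemotherapy lasting about 6 weeks.

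Secondary outcome says the investigators will "calculate the completion rate of the treatment as one of the key secondary outcomes".

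**The concern.** Completing treatment is not the same task for everyone. A colon patient must take eight cycles over 24 weeks. A node-positive rectal patient without prior radiotherapy must take five, one of them with irradiation. By arithmetic that is about 4 × 3 + 6 = 18 weeks. Completion and toxicity may therefore differ between the stage-by-site strata.

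Stratified blocks remove nearly all of that between-stratum variation from the comparison of arms. A plain chi-squared test does not know this. Its variance still includes the spread between strata, so the standard error is larger than the design warrants when the strata differ. What is at stake is some power for a key secondary outcome and for the toxicity comparison, which together describe what the lower dose gains if DFS proves non-inferior.

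**Working it through.** **No planned figure to reproduce.** The only power statement is for DFS. Its 456 events follow from 4 × (1.960 + 0.842)² / (ln 1.30)² = 456.1, which says nothing about completion.

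**How well the strata track the regimen** (Intervention):

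| Stratum | Planned cycles |
|---|---|
| Colon II | 8 |
| Colon III | 8 |
| Rectum II | 8 after prior radiotherapy; 5 with radiochemotherapy if the circumferential margin is positive without prior radiotherapy |
| Rectum III | 5 with radiochemotherapy, unless prior radiotherapy, then 8 |

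The main contrast is rectal stage III against the rest. Margin status and prior radiotherapy also decide the regimen and are not strata, so the match is partial.

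**Inputs.** 463 per arm is from the protocol. Stratum shares of 30/30/20/20 % and the stratum completion rates are assumptions, because the documents give none. Strata are taken as equally split between arms, and the gain as the same number of points in every stratum.

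**Step 1: share of variance within strata.** With shares w and approved-dose rates p, the ratio is R = Σ w·p(1 − p) / [p̄(1 − p̄)].
- A, 75/75/75/55 %: p̄ = 0.71; R = 0.1995 / 0.2059 = 0.969.
- B, 80/70/70/45 %: p̄ = 0.68; R = 0.2025 / 0.2176 = 0.931.
- C, 85/75/70/40 %: p̄ = 0.70; R = 0.1845 / 0.2100 = 0.879.

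**Step 2: actual level of the plain test.** Against the correct variance its critical value is 1.96/√R, giving 1.991, 2.032 and 2.091. The two-sided error rates are about 4.6 %, 4.2 % and 3.6 %.

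**Step 3: power for a gain d = 0.07.** Power = Φ[(d − 1.96·s₀)/s₁], where s₁ = √{[Σ w·p(1 − p) + Σ w·(p + d)(1 − p − d)] / 463}. For the plain test s₀ = √[2·m(1 − m)/463], with m the overall mean rate of the two arms. For the stratified test m(1 − m) is replaced by its within-stratum average.

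Setting A: s₁ = 0.02807.
- Plain: s₀ = 0.02865; Φ[(0.07 − 0.05615)/0.02807] = 0.69.
- Stratified: s₀ = 0.02816; Φ[(0.07 − 0.05519)/0.02807] = 0.70.

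Simulation agrees with these formulas:

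| Setting | Level, plain | Level, stratified | Power at 7 points, plain v stratified | Power at 10 points, plain v stratified |
|---|---|---|---|---|
| Equal rates (70 %) | 5.0 % | 5.0 % | 0.68 v 0.68 | 0.94 v 0.94 |
| A | 4.6 % | 5.0 % | 0.69 v 0.70 | 0.95 v 0.95 |
| B | 4.2 % | 5.0 % | 0.66 v 0.69 | 0.94 v 0.95 |
| C | 3.6 % | 5.0 % | 0.69 v 0.74 | 0.955 v 0.968 |

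**Step 4: other assumptions.** With four equal strata, a common odds ratio and stratified power set near 80 %, the plain test loses up to about 2 points when rectal stage III differs from the rest by up to 27 points. This holds in either direction. The loss is about 5 points at a 40-point difference. Only an extreme 70-point difference (20 % v 90 %) gives a large loss, 56 % v 80 %. At the only completion rates the Background cites for both doses, 95 % v 70 % in a non-randomized breast cancer comparison, both tests have power of about 100 %.

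Toxicity rates were not simulated. The same reasoning applies to them, without a figure.

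**The case against.** The strongest case is that nothing here is wrong. The chi-squared test is standard and valid, and one clause in a condensed article may be refined in an analysis plan that is not shown. A Cochran-Mantel-Haenszel test is itself a form of chi-squared test. Differing rates are not demonstrated either: fewer cycles with added radiotherapy could lower completion, raise it or cancel out. Settings B and C also put a 10-point gap between two strata; if these are the colon strata, they have identical planned treatment. Setting A is closest to the regimen argument, and there the loss is about 1 point. Finally, the Discussion ties the recommendation of the low dose to DFS non-inferiority, and no decision rule rests on the completion p value.

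Most of this stands and limits the point to an efficiency improvement. It does not remove it: the article names a specific test rather than leaving the matter open, and that test does not use the strata the trial takes the trouble to balance.

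A reader might infer more: that the test fails to hold its 5 % level, or that its p values are too large in any case. Neither is supported. The level is held, since the error rate is at or below 5 %. There is no bias, and p values are too large only to the extent that rates differ between strata.

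**Conclusion.** The point holds as a minor one. The planned test for completion and toxicity proportions is valid but mildly conservative if rates differ between the randomization strata. For completion with a 7-point gain, the loss is about 0 to 5 points of power: none with equal rates, about 1 if only rectal stage III differs by 20 points, about 5 at a spread of 85 % to 40 %. It shrinks to at most 1.3 points for a 10-point gain in the same settings and is negligible for larger effects. These sizes rest on assumed stratum shares and rates. The primary DFS analysis is unaffected.

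**What to change.** In Sample size and statistics, replace the plain chi-squared test for completion rate and severe toxicity with a Cochran-Mantel-Haenszel test stratified by the four randomization strata (stage by site). Report the stratum-weighted risk difference between arms with its 95 % confidence interval.

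Also show completion by arm, descriptively, separately for the eight-cycle and five-cycle regimens. This helps whatever the power gain, because one pooled rate mixes different treatment tasks and the strata do not fully separate the regimens.

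The cost is wording only. The strata are recorded at randomization, the named software can run the test, and the risk difference needs only the four two-by-two tables. In the settings examined, the stratified test kept close to 5 % and its power was essentially equal or better.

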## Discussion

It is well established that age is a major risk factor for CRC. According to available statistics, over half of patients with CRC are at least 70 years old, and approximately 43 % of them are at least 75 years old [26]. For stage II/III CRC, adjuvant chemotherapy has been demonstrated to significantly improve survival, and these benefits are not influenced by age [5]. Therefore, there is no doubt that adjuvant chemotherapy should be applied for elderly patients with stage II/III CRC. In reality, however, elderly patients are generally undertreated with chemotherapy because of relatively poor health, and this resulted in a lower participation rate of elderly patients in previous large-scale studies [6] and compromised applicability of those conclusions to elderly patients. Currently, relatively little is known about adjuvant chemotherapy specifically for elderly patients with stage II/III CRC.

The fact that elderly patients obtained no significant benefits from adding oxaliplatin indicated that singe-agent chemotherapy could apply to elderly patients [6]. Compared with intravenous chemotherapy of 5-Fu/Lv, oral administration of capecitabine can remarkably enhance flexibility and compliance, contributing to a higher participation rate for the elderly patients. The major challenge, especially for elderly patients, is to balance the survival benefits and impaired QoL caused by toxic and side effects. Considering the final results of the X-ACT trial, Twelves *et al*. [16] found that patients who experienced fewer toxic and side effects had worse outcomes, implying that dose reduction of capecitabine might compromise the efficacy. Thus far, no published data have identified the long-term efficacy and tolerance of the low-dose strategy.

For capecitabine, the dose of 1,000 mg/m^2^ bid is prescribed frequently in clinical practice and has been reported to be active and well tolerated among elderly patients with breast cancer [17, 27]. Although the response rate was assessed, no long-term results of survival data have been reported for those patients with breast cancer. As for CRC, the low-dose strategy was used in the AVEX trial (ClinicalTrials.gov identifier NCT00484939) for elderly patients with metastatic CRC; however, no comparative analysis about long-time efficacy of this strategy compared with the approved strategy has been published so far. Considering the current gap, we designed this LC-ACEC trial. If our results find compromised long-term efficacy of the low-dose strategy, it might not be an optimal dose for elderly patients with stage II/III CRC although it is widely used at present.

Notably, previous studies reported ethnic differences in the tolerance of capecitabine. Haller *et al*. [28] found that East Asian patients had better tolerance of 5-Fu/capecitabine compared with Caucasian patients. An early study indicated that the thymidylate synthase (*TYMS*) gene 3R/3R variants were more common in Asians [29], and this could affect 5-Fu tolerance. For the elderly Asian patients, however, the pilot Korean study did not observe a satisfactory completion rate for the 1,250 mg/m^2^ dose despite better tolerance for Asians [19]. As for China, a single-arm study including 58 elderly (more than 65 years old) patients with metastatic CRC showed that low-dose capecitabine was well tolerated by those patients [30]. However, that study was limited by the lack of data regarding efficacy and the small sample size. In general, current evidence on the dose of capecitabine for the elderly group of patients is insufficient.

It is worth mentioning that our trial still has limitations. The blinding is limited by the open-label nature of the trial. In addition, time of follow-up is relatively short to achieve long-term outcome given the loss rate caused by high population mobility in this region. Moreover, our trial includes only Chinese patients and this to some degree limits the applicability to other ethnicities because of inter-ethnic differences in tolerance for capecitabine. In summary, the LC-ACEC trial is the first randomized controlled trial to investigate the efficacy and safety of the low-dose capecitabine adjuvant chemotherapy (1,000 mg/m^2^ bid) in elderly patients with stage II/III CRC. If non-inferiority of the low-dose strategy is verified, this can be recommended as a new standard capecitabine adjuvant chemotherapy strategy, specifically for the large group of elderly patients with stage II/III CRC, and this is not only cost-effective but also beneficial for their QoL. The result of this trial will provide evidence on a more specific adjuvant chemotherapy strategy for elderly patients with stage II/III CRC.

